### **3. Secondary endpoint analysis**

The long-term analysis of the quantitative efficacy criteria repeated over time (personalised WOMAC, numeric pain scale, SF12, number of steps, satisfaction) will be carried out using a linear mixed model for repeated measurements (MMRM) taking into account the correlation of the measurements repeated in the same subject (random effect). The fixed effects will be the randomisation arm, operator, time, initial endpoint value and interaction between the time and the randomisation arm. The model will therefore allow us to compare the means adjusted to the absolute variations between the different times of interest (preoperative, 6 months, 1 year) and the initial visit. This analysis technique is consistent with the principle of the intention-to-treat analysis provided that all patients have a baseline value reported for the endpoint.

### **4. Health economics evaluation**

This is a prospective study in which resource consumption by the patients in each arm will be collected in the case report form and evaluated 1) from the Health Insurance perspective, based on the reference nomenclature and prices in force at the end of the study, and 2) from the care-system perspective using the available hospital accounting data.

The resources collected include:

- time period before the intervention by the surgeons in the control group, and by the teams in charge of education and rehabilitation management in the intervention group;
- length of hospital stay and GHM (or the components of the medical unit summary) corresponding to the stay for the intervention;
- length of stay at rehabilitation care facilities;
- consultations and nursing or physiotherapy procedures during the follow-up period;
- imaging studies and medications consumed during follow-up;
- length of time off work or the time taken to resume normal activity.

There are, a priori, no structure costs related to the intervention as this uses existing capacities. However, we can consider designing a budgetary impact and an impact in terms of therapeutic education professionals if this intervention was to be widely used.

#### **Pricing:**

From the Health Insurance perspective: in the control group, the preoperative consultation by the surgeon will be priced at the key-letter rate. The education sessions in the intervention group are not currently priced in the Common Classification of Medical Procedures (CCAM), but we could potentially, by analogy with the pricing of education sessions for diabetic patients, propose 5C for sessions. Admissions to Medical, Surgical and Obstetric (MCO) units will be priced at the GHM rate with any additional supplements (length of stay, mainly). Admissions to rehabilitation care facilities will be priced according to the rates in force at the end of the

study, a fixed daily rate or GHM. Other outpatient consumptions will be priced according to the nomenclature rates corresponding to the reference products for medications. With regard to periods of sick leave for individuals who work, these will be priced in line with the average daily allowance amount.

From the care-system perspective: the main difference is that we are seeking to identify which workload transfers between the acute sector (MCO) and the rehabilitation sector would result from the implementation of an intensive preoperative education programme. Indeed, we can speculate that this programme would enable patients to be discharged earlier (which is neutral in terms of cost from the Health Insurance perspective but not from the hospital perspective) and therefore increase the orthopaedic department activity. Based on the analyses carried out by the hospital medical information departments, we can find out if, on average, a department's revenue is higher than its expenditure. It is therefore possible to determine (again, on average) whether or not a one-day reduction in the length of hospital stay would enable the department to generate revenue in relation to increased activity. The rehabilitation care facility perspective is the simplest as the cost of the intervention involved in the study is equal to the salaries of the individuals involved. Given the absence of pricing for education sessions, there is not currently any revenue to compare.

The calculation from the care-system perspective is therefore particularly interesting as it involves both the financial balance within the orthopaedics department and a potential public decision regarding pricing for the rehabilitation care facility sector.

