### **III.3 - EXPERIMENTAL DESIGN**

We are going to implement a randomised, controlled, multi-centre trial comparing:

- 1) usual treatment provided by the surgeon;
- 2) usual treatment provided by the surgeon combined with standardised and personalised multidisciplinary treatment.

The randomised, controlled trial is considered the gold standard for therapeutic assessment.

The study plan, its implementation, analysis and final write up of the results will be carried out in accordance with the CONSORT statement recommendations [Altman *et al.* 2001] and their extensions for non-pharmacological trials [Boutron, Ravaud *et al.* 2008], and the recommendations of the Medical Research Council for developing and evaluating complex interventions [Craig *et al.* 2008].

The patients randomised into the control group will not have any specific treatment apart from the standard treatment proposed by the surgeon and the messages from a knee arthroplasty guide. This choice allows patients to be in the situation which most accurately represents the current clinical practice and takes into account the lack of a standard treatment having proven to be effective which will be used according to consensus for all the sites.

This choice leads to some methodological issues, as blinding of patients, surgeons and the medical and paramedical team responsible for patient management will not be possible. As a result, there will be a risk of bias in performance and assessment. To take into account these risks, we will:

- a) Systematically collect the co-interventions prescribed in each group (analgesic treatments, physiotherapy prescription, number of consultations with the surgeon) to assess the risk of contamination and performance bias;
- b) Organise an independent assessment by a clinical study technician.

The patients will be informed that the aim of this study will be to compare two treatments for patients in the preoperative period, which are different and possibly effective. To this end, we will explain that they can have either routine care provided by their surgeons, or multidisciplinary care consisting of 4 exercise and therapeutic education sessions while awaiting the surgical intervention, in addition to the routine care.

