#### **VII.6 - SPECIFIC CHARACTERISTICS OF THE STUDY IN RELATION TO THE PATIENT'S USUAL CARE**

The specific characteristics of the study are listed in the table below in relation to what is done as part of the patient's care:

| Description of the procedures                                                 | CARE | STUDY |
|--------------------------------------------------------------------------------------|-------------|--------------|
| Advice given by the surgeon at the orthopaedic consultation                          | X           |              |
| Total knee arthroplasty guide                                                        | X           |              |
| 4 exercise sessions                                                                  |             | X            |
| 4 therapeutic education sessions                                                     |             | X            |
| Preoperative assessment                                                              |             | X            |
| Daily assessment of discharge ability from D1 to D5                                  |             | X            |
| Self-exercise programme and DVD                                                      |             | X            |
| Contact 3 and 12 months after surgery                                                | X           |              |
| Follow-up questionnaires at 6 weeks, 4, 5 and 6 months (by post, email or telephone) |             | X            |

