## **8 Health economics analysis**

The EQ-5D scores will be converted into utilities based on French value tables. The utilities imputed for the periods corresponding to the interval between 2 collections will be multiplied by the corresponding durations to obtain QALYs. The differences in QALYs will be compared between the two groups.

The intervention will be valued on a flat-rate basis based on the time spent by the professionals as described in the protocol and by multiplying the estimated cost of each session by the proportion of patients having undergone the sessions.

Hospital admissions related to the pathology (imputed during the end-of-study meeting) will be valued based on 1) ENCC (French national hospital costs study database) costs and 2) rates. The costs will be estimated for each patient and the average costs in each arm will be compared using non-parametric tests.

The incremental cost-utility ratio will be calculated by comparing the difference in average costs with the difference in average QALYs, with a bootstrap sensitivity analysis.

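### Protocol IX.4 costs the surgeon's preoperative consultation and time for the control arm only, although both arms receive it; applied as written, this understates the programme's incremental cost by one consultation per patient

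*Supplement*

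**What the plan says.** The design section (protocol III.3) describes the experimental arm as "usual treatment provided by the surgeon combined with standardised and personalised multidisciplinary treatment" and tells patients that the sessions come "in addition to the routine care". Inclusion (IV.1) requires that the surgeon has already scheduled the arthroplasty. The table in VII.6 places "Advice given by the surgeon at the orthopaedic consultation" in the care column without tying it to an arm.

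The health economics part of IX.4 is arranged differently. Its first resource item is "time period before the intervention by the surgeons in the control group, and by the teams in charge of education and rehabilitation management", the latter in the intervention group. Under Pricing, for the Health Insurance perspective, "in the control group, the preoperative consultation by the surgeon will be priced at the key-letter rate". The next sentence takes up the intervention group and mentions only the education sessions, for which a tariff of 5C is tentatively suggested. The Health Insurance perspective is the base case, and the one sensitivity analysis singled out concerns the price of the education procedures.

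SAP version 2.0, section 8, costs two things: the programme and pathology-related hospital admissions. On the programme it says "The intervention will be valued on a flat-rate basis based on the time spent by the professionals as described in the protocol", multiplied by session attendance. It mentions no surgeon consultation or surgeon time for either arm.

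**The concern.** In an add-on comparison, a cost that both arms incur cancels from the difference. IX.4 sets out surgeon care and programme care as if they were alternatives: surgeon resources on the control side, programme resources on the intervention side. If an analyst follows that layout, a cost common to both arms is charged to one of them and the difference is pulled down in the programme's favour. The comparator being costed is then not the comparator in the objective.

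What is at stake is a planned secondary analysis: the difference in mean costs and hence the numerator of the cost-utility ratio. Under the protocol, the sign of that difference also helps decide whether a cost-effectiveness analysis is done at all. The two primary endpoints are not affected.

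**Working it through.** The plan gives no incremental cost, cost total or consultation price, so there is no figure to reproduce. The check compares the texts and then does simple arithmetic.

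**Who receives surgeon care before the operation**
- Control arm: the surgeon's usual care (III.3; V.1, control arm).
- Intervention arm: the same usual care plus the programme (III.3). Surgery is already scheduled at inclusion (IV.1), so in both arms the surgeon has been involved before randomisation.
- Surgeons never deliver the programme (VII.2), so their time is not inside its cost.
- The control arm has no extra surgeon consultation by design. III.3 gives controls nothing specific beyond standard care and the guide, and V.1 adds only a pedometer.

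**Who is charged for it**
- Resource list in IX.4: surgeon time named for control; programme team time named for intervention.
- Pricing in IX.4: surgeon consultation named for control; education sessions named for intervention.
- SAP 8: named for neither arm.

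**Effect on the increment.** Let P be the programme price per patient, S the price of the surgeon's preoperative consultation, and R_I and R_C all other mean costs in the two arms.

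- IX.4 as written: (P + R_I) − (S + R_C) = (P − S) + (R_I − R_C).
- S in both arms, or in neither: P + (R_I − R_C).
- Shortfall: S per patient, whatever the other costs are.

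**Size relative to the programme price.** P uses the protocol's tentative 5C and its 4 sessions. S is not given; the range 1C to 2C is an assumption.

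| Reading of 5C | P | P − S at S = 1C | P − S at S = 2C | Shortfall S/P |
|---|---|---|---|---|
| per session | 4 × 5C = 20C | 19C | 18C | 1/20 = 5% to 2/20 = 10% |
| all sessions together | 5C | 4C | 3C | 1/5 = 20% to 2/5 = 40% |

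On the SAP 8 list, S is in neither arm. The programme contribution is then P without deduction, and the shortfall from this source is 0.

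**The case against.** The strongest reply is that the SAP governs the analysis and has already disposed of the issue: section 8 charges no surgeon item to either arm, which is one of the two acceptable treatments. That is correct for the SAP's own list. A reader might infer that section 8 brings surgeon time back in by referring to the protocol for professionals' time. It does not: that sentence is about the programme and its sessions, which surgeons do not deliver. What the reply does not settle is which cost list applies. Section 8 does not say that it replaces IX.4. The SAP change log describes the edit to section 8 only as an EQ-5D correction. The SAP summary keeps both the Health Insurance and care-system perspectives, yet section 8 does not name consultations, physiotherapy, imaging, medications or time off work, all of which IX.4 collects. Someone completing the costing would naturally return to IX.4.

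A second reply is that control-only charging is inferred from silence. IX.4 speaks of resource use in each arm, its list is open-ended, and III.3 undertakes to "Systematically collect the co-interventions prescribed in each group (analgesic treatments, physiotherapy prescription, number of consultations with the surgeon"). This has some force: no sentence says that the intervention arm's consultation goes uncosted. But the same pairing appears in the resource list and again in the pricing, so it is unlikely to be a slip in one sentence. Nor does the co-intervention count clearly capture the consultation at issue. The preoperative visit records co-interventions since enrolment (VII.3.1), whereas surgery is scheduled before enrolment.

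A third reply is that the percentages rest on an assumed price and on a tariff that the SAP does not use. That stands, and it limits how the figures may be read.

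**Conclusion.** The point holds in conditional form. IX.4 is at odds with the protocol's own design, and if its cost rule is applied as written, the programme's incremental cost in the base-case Health Insurance perspective is understated by one surgeon consultation per patient. The direction is certain and favours the programme. The amount is not: 5% to 10% or 20% to 40% of the programme price, depending on what 5C covers and on the assumed 1C to 2C consultation. Under SAP 8 alone it is zero. The current protocol and SAP therefore imply different increments, and neither states how the common item is to be handled.

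Three stronger conclusions are tempting but unsupported:
- That the planned analysis as a whole understates the cost. SAP 8 contains no such charge.
- That the cost difference or cost-utility ratio shifts by these percentages. They are shares of programme price only; the difference also includes admissions and other costs that the documents do not quantify.
- That in the care-system perspective the full cost of surgeon time is lost. The pricing text for that perspective discusses workload transfers, length of stay and programme salaries, and charges no surgeon item.

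This is a modest inconsistency in a secondary analysis, worth correcting because the correction is simple and removes a bias of known direction.

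**What to change.** Amend the resource list and the Pricing text in protocol IX.4 to say that the surgeon's preoperative consultation and time are usual care common to both arms before randomisation and are omitted from both, with the programme cost added in the intervention arm. Charging the item identically to both arms is an acceptable alternative and gives the same difference. Put the same sentence in SAP section 8, and state there which cost list governs the analysis, so that the two documents agree.

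Omission from both arms is the simpler choice. It needs no new data and no consultation price, and it does not rely on co-intervention records that may miss a consultation held before enrolment. The cost is one or two sentences in each document. The programme will look dearer by one consultation per patient than it would under IX.4 as written, and unchanged relative to the SAP 8 list.

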### **Health economics evaluation.**

The intervention costs (from the Health Insurance perspective for the basic calculation) will be compared. In the event that the most expensive strategy is the one which provides the best functional outcome and quality of life, we will carry out a cost-effectiveness analysis. The values will be taken from the EuroQol questionnaire. The base ratio estimation will be completed with a sensitivity analysis (particularly on the pricing of education procedures) and a bootstrap estimation of confidence intervals.

## **X - SAFETY ASSESSMENT**

### **X.1 - DEFINITIONS**

According to Article R1123-39 of the French Public Health Code:

- **Adverse event:**

Any harmful manifestation occurring in an individual taking part in a biomedical research study, regardless of whether or not the manifestation is related to the study.

- **Adverse event** in a study not involving a product mentioned in Article L.5311-1 (medicinal products, biomaterials and medical devices, in vitro diagnostic medical devices, labile blood products, organs, tissues, cells and products of human or animal origin, and cellular products for therapeutic purposes).

Any adverse event due to the study.

- **Serious adverse event or effect:**

Any adverse event or effect that leads to death, is life-threatening for the individual taking part in the study, involves hospital admission or an extended hospital stay, causes significant or permanent incapacity or disability, or leads to a congenital abnormality or malformation.

- **New information:**

Any new safety information that may lead to a reassessment of the risk-benefit ratio of the study, or which may be enough to consider making amendments to study-related documents, to the way the study is conducted and, where applicable, to the way the product is used.

## **X.2 - DESCRIPTION OF THE SAFETY ASSESSMENT PARAMETERS**

The study-specific procedures are as follows:

- 4 exercise sessions;
- 4 therapeutic education sessions;
- preoperative assessment;
- daily assessment of discharge ability from D1 to D5;
- self-exercise programme and DVD;
- follow-up questionnaires at 6 weeks, 4, 5 and 6 months (by post, email or telephone).

This is a multidisciplinary programme combining therapeutic education and exercises, with the exercise intensity being adapted to the patient's pathology and age, under the supervision of a physiotherapist. We have no known or reported factors regarding the risks related to the education programme.

The adverse events that may occur during the study are mainly related to the assigned treatment strategies.

- Main adverse events related to the education programme
  - ✓ no known or reported evidence on this subject
- Main adverse events related to the exercise programme
  - ✓ increase in exercise-related pain

- ✓ exercise-related injuries to muscles (cramps, elongation), ligaments (sprain) and joints (effusion). These are minor, non-progressive injuries which are quick to heal, as the exercise intensity will be adapted to the patient's pathology and age, under the supervision of a physiotherapist.

If any events occur, the patients will be assessed by the doctor in charge of the study for their treatment.

The study doctor will record adverse events (AEs) from the date on which the informed consent form is signed, for the whole duration of the patient's participation in the study, on the adverse events page of the case report form.

As this is a biomedical research study classified as "risk A", i.e. for which there is a negligible **additional risk expected for the study**, no **serious** adverse events are expected through the course of the study.

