## VII.2 - INTERVENTION PROTOCOL

Patients will be seen at the day hospital (third-category rehabilitation care facilities) on four occasions over two weeks, at least two months before the intervention.

**Intervention:** The multidisciplinary programmes will be carried out at the Rehabilitation Department at Cochin Hospital and Clermont-Ferrand Hospital and at the Lariboisière Rheumatology Department. The programme is prepared according to the Medical Research Council Guidance recommendations for developing and evaluating complex interventions (Craig *et al.* 2008). This requires expert consensus, preparation of an information booklet for patients, and training for trainers. All investigators have vast experience in treating patients with TKA. The intervention is never carried out by surgeons, which prevents the risk of contamination.

Patients in the intervention group will receive four 1.5-hour supervised group sessions (4 to 6 patients) consisting of 30 minutes of education and 1 hour of physical exercise at least two months before surgery with two sessions per week for two consecutive weeks.

Transfers to the four multidisciplinary treatment sessions will be covered by the study.

Patients in the control group will receive the usual information and advice given by the orthopaedics department at each centre in line with their usual practice and a knee arthroplasty guide (Annex 10), as well as a pedometer to measure the number of steps (Annex 9).

The multidisciplinary programme is standardised and personalised (Annex 7). For the educational part, the four sessions will be divided up as follows:

- The first session led by a physiotherapist deals with the role of physical activity and exercises before undergoing the arthroplasty and walking after the procedure. It will be checked that the pedometer is used properly. For active patients, the aim will be to maintain the level of activity. For sedentary patients, the aim will be to gradually increase the number of steps measured using the pedometer by 20% before the surgery.

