### **VII.3 - FOLLOW-UP VISITS AFTER THE INTERVENTION**

#### **VII.3.1 - PREOPERATIVE VISIT (V1)**

At the preoperative visit, which will take place one or two days before the surgery, the following information will be collected in the electronic case report form:

- Professional status;
- Number of steps measured by the patient in the week (7 days) before this visit;
- Co-interventions since the enrolment visit;
- Adverse events.

Patients will fill in a self-assessment card including assessment of the following:

- knee pain over the past 48 hours (numeric scale);
- function according to the WOMAC scale and the personalised section;
- quality of life (MOS SF-12);
- adaptation of environment.

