## **7 Tolerance analysis**

### **7.1 Adverse events**

#### **7.1.1 Definition**

Any adverse events spontaneously reported by patients at telephone follow-up visits or recorded at a visit will be taken into account. The following information will be collected for each adverse event:

- its intensity (severity): mild, moderate or severe;
- its treatment, if any;
- its duration;
- its causality, as determined by the investigator (not assessable, unlikely, possible, likely, certain, or unrelated to the investigational treatment).

The adverse event rate will be analysed at month 12.

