#### **7.1.2 Analysis**

Adverse events and their characteristics will be described in the form of sample sizes and percentages by treatment arm. Fisher's exact tests will be used to compare the two treatment arms in terms of the proportion of patients with at least one AE/SAE and the proportion of patients with at least one SAE. The total number of AEs/SAEs and SAEs will also be described for each arm.

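### The month-12 adverse-event test cannot separate risk from detection, because before surgery only the intervention arm has four extra supervised contacts at which events can be noticed

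*Supplement*

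**What the plan says.** Protocol X.1 defines an adverse event as any harmful manifestation, related to the study or not. X.2 sets the start of recording for all patients: "The study doctor will record adverse events (AEs) from the date on which the informed consent form is signed". It names increased exercise-related pain and muscle, ligament and joint injuries as the main events of the exercise programme, calls them minor and quick to heal, and continues: "If any events occur, the patients will be assessed by the doctor in charge of the study for their treatment".

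The study schedule in section VII lists AEs at V1, V2, month 3, month 6 and month 12, for both arms alike. V1 is therefore the only scheduled collection before surgery: "At the preoperative visit, which will take place one or two days before the surgery".

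Under VII.2 the intervention arm is also seen at the day hospital "on four occasions over two weeks, at least two months before the intervention". Controls receive usual advice, a guide and a pedometer (V.1, control arm), and no study contact is scheduled for them between enrolment and V1.

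SAP v2.0, section 7.1.1, describes what counts: "Any adverse events spontaneously reported by patients at telephone follow-up visits or recorded at a visit will be taken into account". It adds: "The adverse event rate will be analysed at month 12". Section 7.1.2 then states: "Fisher's exact tests will be used to compare the two treatment arms in terms of the proportion of patients with at least one AE/SAE". A second test covers patients with at least one SAE.

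**The concern.** The proportion that enters the test is true risk multiplied by the chance that an event is noticed and recorded. Before surgery that chance may differ by arm. A cramp, effusion or pain flare in an intervention patient can come to light at a session led or supervised by study staff and reach the AE page. The same event in a control has to be remembered and mentioned at V1, two months or more after the sessions would have taken place. By the protocol's own description these injuries heal quickly, so they are easily forgotten. They can also occur in any osteoarthritic knee awaiting replacement, and X.1 counts them whether or not they relate to the study.

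Neither document provides an identical AE question for both arms, a field for where an event was detected, a split between preoperative and postoperative events, or a sensitivity analysis. A significant excess in the intervention arm could therefore mean harm, closer observation, or both. The programme's named risks arise before surgery, which is where the asymmetry lies. No independent monitoring committee is planned (X.4.2), so this comparison is the main between-arm safety evidence.

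**Working it through.** The documents give no AE rate, no detection rate and no power for the AE tests, so there is no planned figure to reproduce.

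**Inputs from the documents.** 150 patients per arm (IV.3). Tests are two-sided (SAP 4.1). That section sets 5% for secondary endpoints and states no level for the AE tests; I take 5%. Sessions occupy two weeks, at least two months before surgery (VII.2), and start no more than one month after enrolment (VII.1).

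**Assumptions.** True preoperative risk r is equal in both arms. Detection before surgery is d, which may differ by arm. Postoperative AE risk q is recorded equally in both arms and is independent of preoperative events.

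**Formula.** Recorded proportion = 1 - (1 - r·d)(1 - q). Fisher rejection probabilities come from full enumeration of the two binomials.

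**Equal detection.** At a recorded rate of 40% in both arms the test rejects in 3.9% of trials. Over r = 10-40% and q = 0-60% the figure is 3.3-4.3%.

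**Detection gap over the whole wait** (r = 20%; control d = 50%):

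| d, intervention | q | Recorded, intervention v control | False difference | Rejection |
|---|---|---|---|---|
| 80% | 20% | 32.8% v 28.0% | 4.8 points | 12% |
| 80% | 40% | 49.6% v 46.0% | 3.6 points | 8.5% |
| 90% | 20% | 34.4% v 28.0% | 6.4 points | 19% |
| 90% | 40% | 50.8% v 46.0% | 4.8 points | 12% |

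For example, the third row is 1 - (1 - 0.20 × 0.90)(0.80) = 0.344 against 1 - (1 - 0.20 × 0.50)(0.80) = 0.280. At least 95% of the rejections in this table point to harm. Widening to r = 15-30% and adding a 90% v 70% gap gives 5-36%, so the result is driven by the inputs.

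**Detection gap confined to the session weeks.** Let f be the share of the wait in which detection is 90% v 50%, with 50% in both arms otherwise and events spread evenly. Average detection in the intervention arm is then 0.9f + 0.5(1 - f).

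- Two of 10 weeks: 0.9 × 0.2 + 0.5 × 0.8 = 0.58. With r = q = 20%, recorded rates are 29.3% v 28.0%, and the test rejects in 4.3%.
- Over waits of 10-12 weeks, r = 15-30% and q = 20-40%, the false difference is 0.6-1.9 points and rejection is 4.0-5.0%, no higher than nominal.
- If the sessions also pick up everything in the preceding month (6 of 14 weeks), average detection is 0.67. With r = q = 20%, recorded rates are 30.7% v 28.0%, and rejection is 6.4%. Over the same r and q, rejection is 5-9%.

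**Cost of testing only shared-contact events.** Suppose true harm: preoperative risk 35% v 20%, q = 20%. With 50% capture in both arms the recorded rates are 34% v 28% and power is 17%. With full capture they are 48% v 36% and power is 52%.

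**The case against.** A reader might infer that AE collection is scheduled more often in the intervention arm. It is not: the schedule lists the same AE contacts for everyone, and no section sets AE collection at the sessions. They are opportunities for detection only.

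Nor does the sentence on assessment by the study doctor establish an intervention-only channel. It follows the list of exercise risks but is not expressly limited to one arm, and the recording rule in X.2 makes no distinction.

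SAP 7.1.1 counts events recorded at a visit. The protocol calls the programme contacts sessions, so the test may already be meant to use shared contacts only. That reading is open, but the SAP does not state it, and nothing in the data would identify where an event was found.

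It would also be too strong to say that everything known about controls before surgery rests on one recall. All patients receive a diary for treatments taken, co-interventions are collected at V1 in both arms, and pain is measured in both arms at enrolment and V1. These give context but do not equalise AE detection.

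Finally, postoperative collection is symmetric and dilutes any bias, SAEs are less likely to be missed, and AEs are not an efficacy endpoint. All of this limits the size. It does not remove the mechanism.

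**Conclusion.** The point holds as a cheap improvement to the safety analysis. The documents show an extra preoperative opportunity for detection in one arm and a pooled month-12 test that cannot tell detection from risk. Any resulting bias would run towards apparent harm from the programme.

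The documents do not support saying that the test is seriously inflated. With equal true risk, rejection runs from 4-5% (gap confined to the two session weeks), through 5-9% (sessions also pick up the preceding month), to 8.5-19% (true risk 20%, capture 80-90% v 50% throughout the wait, postoperative rate 20-40%). The larger figures need events bunched around the sessions or a detection advantage lasting the whole wait, and neither is documented. All risk and capture values are assumptions.

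A reader might also conclude that session-detected events should leave the main test. That does not follow: it could hide real harm, as the 17% against 52% power shows.

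**What to change.** - **At V1:** put the same closed question to both arms, covering new or increased knee pain and muscle, ligament or joint injury since enrolment.
- **eCRF AE page:** add a field for where the event was detected.
- **SAP 7.1:** keep the all-source Fisher test and state its significance level. Show preoperative and postoperative AEs separately by arm. Add a sensitivity Fisher test limited to events obtained at contacts common to both arms (V1, V2, months 3, 6 and 12). List session-detected events descriptively.

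The cost is one question, one field and a few lines of SAP text. Solicited questioning will raise the count of minor AEs in both arms. No event leaves the main safety comparison. For patients already past V1, the SAP changes can still be applied wherever AE dates or sources allow.
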